## Abstract

**BACKGROUND:**

Enteral nutrition therapy in the early postoperative period is essential for patients with esophageal cancer following esophagectomy. HINEX® E-gel LC is an oligomeric formula with various nutrients, including dietary fiber pectin. It is expected to reduce symptoms, such as diarrhea, resulting in improved adherence and a decreased rate of weight loss. However, no reports have examined the adherence to or efficacy of nutritional support therapy using HINEX® E-gel LC after esophagectomy.

**METHODS:**

This is a single-institution, single-arm phase II trial. We plan to recruit 32 patients with esophageal cancer who have undergone minimally invasive esophagectomy (MIE) and place an enteral feeding tube. Enteral feeding is to be initiated on the second postoperative day, and the patient is to remain on enteral feeding at 300 kcal/day after discharge. The primary endpoint is adherence to enteral nutrition with HINEX® E-gel LC for up to 2 months postoperatively. The secondary endpoint is the association between the adherence to HINEX® E-gel LC and each nutritional parameter, such as hematological examination, body weight, and psoas muscle.

**DISCUSSION:**

Although enteral nutrition is usually initiated in the early postoperative period after esophagectomy, the use of fat-containing digestive agents in the early postoperative period is a novel approach. To the best of our knowledge, this study is the first to evaluate the safety and nutritional status of early postoperative enteral nutrition using fat-containing digestive agents after MIE. Efficient nutritional support therapy using fat-containing digestive agents is expected to be especially useful after esophagectomy when oral intake is significantly decreased.

## INTRODUCTION

Malnutrition due to decreased nutritional intake is one of the most common postoperative disorders following esophagectomy for esophageal cancer; it is a prognostic factor for esophageal cancer [1–3]. Sarcopenia, a condition in which skeletal muscle mass decreases with age, is associated with poor postoperative outcomes [4, 5].

Enteral nutritional therapy in the early postoperative period is widely used to prevent malnutrition after esophagectomy. However, adherence to postoperative nutritional supplementation remains an issue. Nutritional support therapy with Lacol® NF, a polymeric formula, has been reported to maintain adherence to dosing, which contributed to lower weight loss rates for patients with gastric cancer [6]. In contrast, abdominal discomfort and diarrhea caused by oral nutritional supplementation affect adherence in patients who undergo gastrectomy [7, 8].

HINEX® E-gel LC is an oligomeric formula with various nutrients adjusted with reference to the “Dietary Reference Intakes for Japanese, 2020” [9]. Compared with conventional nutritional supplements, the inclusion of dietary pectin is expected to reduce symptoms such as diarrhea, resulting in improved adherence and a lower rate of weight loss. In addition, compared to the component nutrients, dissolving the drug is not required, and it is easy to use. However, no reports have examined the adherence to or efficacy of nutritional support therapy with this formulation after esophagectomy.

This study aimed to evaluate the adherence to HINEX® E-gel LC for patients who underwent minimally invasive esophagectomy (MIE) for esophageal cancer.

## METHODS AND DESIGN

### Hypothesis

This study hypothesizes that HINEX® E-gel LC in an oligomeric formulation can be safely administered as enteral nutrition after MIE.

### Study design, endpoints, and period

This is a single-center, single-arm, phase II trial to evaluate the safety and nutritional status of postoperative enteral nutrition using an oligomeric formula nutrient (HINEX® E-gel LC) in patients with esophageal cancer undergoing MIE. The primary endpoint is adherence to enteral nutrition with HINEX® E-gel LC for up to 2 months postoperatively. The secondary endpoint is the association between the adherence to HINEX® E-gel LC and each nutritional parameter, such as hematological examination, body weight, and psoas muscle. The expected total duration of patient enrollment is 2 years, and the follow-up period is 6 months.

### Patient selection and enrollment criteria

#### Inclusion criteria

The inclusion criteria will be as follows: (i) age is over 18 years old at the registration date; (ii) the clinical stage was I, II, or III according to the Japanese Classification of Esophageal Cancer, 12th edition (based on esophagogastroduodenoscopy, computed tomography, and positron emission tomography); (iii) an Eastern Cooperative Oncology Group performance status of 0, 1, or 2; (iv) oral intake is feasible preoperatively; (v) esophagectomy is expected within 60 days from the date of registration; (vi) oral intake is expected for 3 months after esophagectomy; and (vii) written informed consent obtained.

#### Exclusion criteria

The exclusion criteria will be as follows: (i) history of hypersensitivity to any element of this nutritional supplement; (ii) allergies to any of the material (especially soy and gelatin) in the test nutritional product, HINEX® E-Gel LC; (iii) difficulty in obtaining consent because of dementia or psychiatric diseases that require treatment; (iv) use of steroids or immunosuppressive drugs; (v) infectious disease requiring systemic treatment; and (vi) any other information deemed inappropriate by the investigator.

#### Discontinuing criteria

Protocol treatment will be discontinued if the following criteria are met: (i) requesting treatment discontinuation because of illness or other reasons; (ii) fasting >30 days after surgery; (iii) undergoing non-curative resection; (iv) recurrence of the primary disease during the study period; (v) death during protocol treatment; and (vi) withdrawal of patient consent.

Even after discontinuation of protocol treatment, unless participation in the study is discontinued, investigation and observation as provided for in the research will be conducted until the end of the follow-up period.

### Sample size

In this trial, the sample size for analysis was 32 patients. In a phase III clinical trial of Twinline® [10], a digestive-form nutritional supplement, 167 patients with gastrointestinal diseases requiring enteral nutrition were participated. Of the 167 patients, 8 had dose reductions due to adverse effects and 13 discontinued due to adverse effects under the condition that the dosing period was 5 days or longer. The main adverse events that occurred in this study were diarrhea, abdominal pain, and abdominal distention. Of the 167 patients, 146 were able to complete the 5-day dosing, or an estimated 87.4%. In this trial we have planned, we expect the completion rate to be at 2 months, which is the typical duration of feeding tube use in clinical practice. If 23 of the 25 cases in the analysis were completed, the completion rate is estimated to be 92.0%, with 95% confidence intervals of 74% and 99%. This setting was made based on the assumption that the use of HINEX® E-gel LC would have an additional effect on the conventional clinical trial of Twinline®. After examining 25 patients and estimating the exclusion of approximately five patients because of complications such as anastomotic leakage and the discontinuation of approximately two patients due to cancer recurrence, the sample size for this trial was calculated to be 32 patients. The above settings were also estimated based on the number of operations per year at our hospital, as we estimated the duration of the trial to be approximately 1 year. The sample size was also calculated using JMP® version 14.2 (SAS Institute Inc., Cary, NC, USA).

### Treatment

The eligibility assessment for this study is shown in Figure 1. All patients underwent MIE, including robotic surgery, in the prone position. After the thoracic procedure, gastric conduit reconstruction via the retrosternal route and feeding tube placement is performed, and a feeding tube is placed. Enteral feeding is initiated on the second postoperative day, and the amount of enteral feeding is gradually increased while observing the abdominal symptoms. Oral intake begins 1 week after esophagectomy, and the amount of enteral feeding is tapered off. After discharge from the hospital, the patient will continue to receive enteral feeding of 300 kcal/day at home, and the tube will be removed at an outpatient hospital when oral intake is considered sufficient. For enteral nutrition support at home, we will ask the patients to write down what they have eaten and weight changes in order to collect accurate information, which we will use to provide nutritional support. Since enteral nutrition for approximately 2 months after esophagectomy is common in previous studies, we will observe the completion rate at 2 months in this study as well. The purpose of this study is to investigate patient compliance with administration of the nutritional products; therefore, a self-interruption of more than 2 weeks is not considered a protocol deviation, but it will be recorded as a failure to the study.

### Participant timeline

The schedule for conducting the observations, examinations, and evaluations of the participants is presented in Table I. The investigator will conduct observations and examinations according to the schedule.

### Follow-up and assessment

The percentage of patients who can continue taking HINEX® E-gel LC daily for up to 2 months after surgery will be evaluated. The occurrence of illness and other symptoms will be evaluated as part of the safety assessment (gastrointestinal symptoms related to protocol treatment: diarrhea, constipation, vomiting, and others) and the duration of use of HINEX® E-Gel will be evaluated. The Common Terminology Criteria for Adverse Events (CTCAE) ver. 5.0 will be used to evaluate illness.

The following secondary endpoints will be evaluated as nutritional indicators until 6 months postoperatively: (i) Eastern Cooperative Oncology Group (ECOG)-Performance Status (PS) (2, 3, and 6 months postoperatively); (ii) nutritional index parameters based on blood samples (preoperatively, 2, 3, and 6 months postoperatively; total protein [TP], serum albumin [ALB], total lymphocyte count, total cholesterol, transthyretin, hemoglobin [Hb], C-reactive protein [CRP]); (iii) body weight loss rate (BWL) at 2, 3, and 6 months postoperatively (%BWL = Preoperative weight | Postoperative weight/Preoperative weight × 100 [%]); (iv) skeletal muscle mass using computed tomography (CT) images (preoperatively and 6 months postoperatively); and (v) measurement of body composition and muscle mass using bioelectrical impedance analysis (BIA) (preoperatively, 2, 3, and 6 months postoperatively).

Additionally, patient background (sex, age, height, weight, medical history, family history, drinking history, and smoking history) and surgical information (operative procedure, operative time, blood loss, and postoperative complications) were evaluated.

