### Evaluation and reporting of adverse events

The physician will document all diseases that occur from the time the trial product is used to the date of completion of its use in a case report form and submit it to the research office. The investigator will observe the patients until the disease is resolved or until two weeks after the end of their participation in the clinical research.

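### The GI safety assessment is described as treatment-related symptoms while all events are recorded; report GI symptoms regardless of cause, because relatedness cannot be checked in this design

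*Protocol article*

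**What the plan says.** All references are to the protocol article.

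- **Hypothesis.** The study hypothesis is that the product "can be safely administered as enteral nutrition after MIE". Safe use is thus the claim under study.
- **Study design, endpoints, and period.** The design is stated as follows: "This is a single-center, single-arm, phase II trial to evaluate the safety and nutritional status of postoperative enteral nutrition". There is no comparator.
- **Follow-up and assessment.** The safety sentence opens broadly: "The occurrence of illness and other symptoms will be evaluated as part of the safety assessment". A parenthesis then gives its content: "gastrointestinal symptoms related to protocol treatment: diarrhea, constipation, vomiting, and others". Grading follows: "The Common Terminology Criteria for Adverse Events (CTCAE) ver. 5.0 will be used to evaluate illness". Postoperative complications are listed separately, as surgical information.
- **Evaluation and reporting of adverse events.** The recording rule reads: "The physician will document all diseases that occur from the time the trial product is used to the date of completion of its use". No causality condition is attached.
- **Sample size.** On the phase III reference trial of Twinline: "The main adverse events that occurred in this study were diarrhea, abdominal pain, and abdominal distention".

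**The concern.** The set of events recorded and the set described for GI safety differ by one qualifier: relatedness to protocol treatment. If the parenthesis is followed as written, an episode of diarrhea or vomiting enters the GI safety rate only after someone has decided that the feed, and not the operation, caused it.

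This trial gives that decision little to stand on. Under Treatment, every patient has an esophagectomy with gastric conduit reconstruction, starts tube feeding on postoperative day 2 and resumes eating at one week. All three can produce the same symptoms over the same weeks, and no control group shows what would have happened without the product.

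Safe administration is the hypothesis, and fewer symptoms such as diarrhea are part of the product's rationale in the Introduction. GI symptoms are therefore the central tolerability result, and that result should not rest on a judgement that cannot be verified.

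**Working it through.** **1. The plan's own figure.** The one confidence interval in the article, under Sample size, is for 23/25 = 92.0%, given as 74% to 99%. The exact (Clopper-Pearson) interval is 73.97% to 99.02%, so it reproduces. It concerns completion and has no bearing on this point, but it shows that exact intervals fit the article's own figures.

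**2. The two passages side by side.**

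| | Follow-up and assessment | Evaluation and reporting of adverse events |
|---|---|---|
| Scope | Illness and other symptoms, then GI symptoms in a parenthesis | All diseases |
| Causality condition | Related to protocol treatment | None |
| Rule for judging causality | None printed | Not needed |

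I read diseases here as adverse events including symptoms, because that is the subject of the section. On that reading an all-cause GI rate can be derived for the period of product use, but nothing commits the trial to reporting it.

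**3. What a relatedness filter does.** Let A be the number of patients with a GI symptom from any cause, T the number whose symptom the product truly caused, and R the number judged related.

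- Patients counted in R are a subset of those counted in A, so R ≤ A always.
- Let s be the share of T judged related, and u the share of the other A − T judged related. Then R = sT + u(A − T), and the error is R − T = u(A − T) − (1 − s)T.
- The error is positive when surgical symptoms are blamed on the feed more often than feed symptoms are blamed on surgery, and negative in the reverse case. With assumed A = 10: if T = 8 and R = 5 the error is −3; if T = 5 and R = 8 it is +3. A single-arm trial observes neither s nor u.

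**4. Illustration of the gap between R and A.** The documents give no GI rate and no attribution share, so both are assumed here and shown over a range. The two denominators are the 25 analysable patients and the 32 planned under Sample size. Intervals are exact 95%, and counts are rounded to whole patients.

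| n | Assumed all-cause rate | All-cause count (95% CI) | Related count if about 75% attributed | Related count if about 50% attributed |
|---|---|---|---|---|
| 25 | 40% | 10/25 = 40% (21% to 61%) | 8/25 = 32% (15% to 54%) | 5/25 = 20% (7% to 41%) |
| 25 | 20% | 5/25 = 20% (7% to 41%) | 4/25 = 16% (5% to 36%) | 2/25 = 8% (1% to 26%) |
| 32 | 40% | 13/32 = 41% (24% to 59%) | 10/32 = 31% (16% to 50%) | 6/32 = 19% (7% to 36%) |
| 32 | 20% | 6/32 = 19% (7% to 36%) | 5/32 = 16% (5% to 33%) | 3/32 = 9% (2% to 25%) |

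At n = 25 the gap runs from 20 − 16 = 4 to 40 − 20 = 20 percentage points. It is set entirely by the assumed inputs and estimates nothing about this trial.

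**5. Primary endpoint.** Under Treatment, a self-interruption of more than two weeks counts as a failure with no cause required. Completion therefore does not depend on causality judgements.

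**The case against.** The strongest reply is that the parenthesis is descriptive: it names the kind of symptom expected with tube feeding and excludes nothing. The main clause covers illness and symptoms in general, the list is open-ended, and the adverse event section records everything. Causality rules and safety tables usually sit in the full protocol or analysis plan, which are not shown.

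Much of this stands, and it rules out several stronger readings that a reader might infer:

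- **That only related symptoms will be counted.** The article never says so. The sentence is ambiguous between all-cause and related-only.
- **That GI toxicity is biased downward, in the product's favour.** A related-only count cannot exceed the all-cause count, but the all-cause count includes surgical symptoms and is not a measure of product toxicity. Against symptoms truly caused by the product, misattribution can go either way. Feeding is increased under observation of abdominal symptoms, so a physician may just as readily blame the feed.
- **That abdominal pain and distention are lost, or that comparison with the Twinline trial is ruled out.** The open-ended list and the adverse event section both capture them. The article uses Twinline for its completion figure, plans no comparison of symptom profiles, and does not show whether the reference counts were all-cause.
- **That the main result is at risk.** The primary endpoint is untouched.

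The reply does not remove the qualifier itself. This is wording the article states, not detail it leaves out. Recording all events makes the all-cause rate available, but it leaves the choice of headline open until the data have been seen.

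**Conclusion.** The point holds as an inexpensive improvement to the safety summary. The article attaches a relatedness qualifier to its GI safety assessment and records all events elsewhere without one. Followed as written, the qualifier makes the GI rate depend on a judgement this design cannot check. The resulting rate would be at or below the all-cause rate by an unknown amount, and its error against product-caused symptoms has no known direction.

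No size can be given, because the documents contain no GI rates. The conclusion rests on two assumptions: that the parenthesis would guide the summary, and that the adverse event section's diseases include GI symptoms. If the full protocol or analysis plan already commits to all-cause reporting, only the wording of the article needs aligning.

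**What to change.** Reconcile the two sections by removing the relatedness qualifier from the main safety summary. Suggested wording:

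> The main safety summary will give, among all patients who received any HINEX E-gel LC, the number and proportion with each of diarrhea, constipation, vomiting, abdominal pain, abdominal distention and other GI symptoms, regardless of causality, by worst CTCAE v5.0 grade during product use, with exact 95% confidence intervals. Events judged by the investigator to be related to the product will be shown as a supplementary classification.

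Naming abdominal pain and distention adds the two main Twinline events that now fall under the general category. Using every patient who received product as the denominator keeps in those who later leave the set of 25 through complications or recurrence.

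The cost is one sentence in the protocol and the analysis plan. No new data are needed, since the adverse event section already has these events recorded. The downside is that the headline rate will be higher and will include some symptoms caused by surgery, which the report should say.

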### Statistical methods

The primary analysis will be to calculate the completion rate of enteral nutrition at 2 months postoperatively, which is the primary endpoint of this clinical study, and to estimate the 95% confidence interval. Efficacy will be analyzed as a secondary endpoint.

### Evaluation and reporting of adverse events

The physician will document all diseases that occur from the time the trial product is used to the date of completion of its use in a case report form and submit it to the research office. The investigator will observe the patients until the disease is resolved or until two weeks after the end of their participation in the clinical research.

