## DISCUSSION

Surgical resection is a standard treatment for patients with esophageal cancer. However, esophagectomy is associated with higher morbidity and mortality rates than other gastrointestinal surgeries. Recently, MIE has become the standard surgical procedure for esophageal cancer worldwide and has been reported to reduce postoperative respiratory complications, shorten hospital stays, and improve quality of life compared to open esophagectomy [11]. Therefore, overcoming postoperative malnutrition caused by decreased nutritional intake after MIE is important.

Sarcopenia is associated with poor postoperative outcomes in various cancer types [4]. Therefore, the completion rate of enteral nutrition after surgery may be related to improved long-term postoperative outcomes. Hinex® E-Gel LC used in this study is a digestive-form liquid food containing dietary fiber pectin. This food was designed considering hydration, and the amount of water that could be consumed per 100 kcal was adjusted to 110 mL. Although enteral nutrition is usually initiated in the early postoperative period after esophagectomy, the use of fat-containing digestive agents in the early postoperative period is a novel approach. The novelty of this study is the use of fat-containing digestive-form in the early postoperative period. To the best of our knowledge, this study is the first to evaluate the safety and nutritional status of early postoperative enteral nutrition using fat-containing digestive agents after MIE. Efficient nutritional support therapy using fat-containing digestive agents is expected to be especially useful after esophagectomy when oral intake is significantly decreased.

Long-term enteral nutrition after MIE reduces skeletal muscle loss [12], while placement of an enterostomy in the jejunum increases the risk of bowel obstruction [13]. In this trial, we planned gastric conduit reconstruction through the retrosternal route and feeding tube placement from the antrum of the gastric tube. In addition, a round ligament of the liver is interposition, and a tube is fixed to the abdominal wall to prevent peritonitis after removing the feeding tube [14, 15].

Through this phase II trial, we aim to determine the safety and nutritional status of postoperative enteral nutrition using the oligomeric formula nutrient HINEX® E-gel LC in patients with esophageal cancer undergoing MIE.

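### Recording of new adverse events stops on the last day of product use, so events starting after tube removal, or after early stopping, fall outside the stated window

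*Protocol article*

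**What the plan says.** All references are to the Protocol article.

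- **Recording window** (Evaluation and reporting of adverse events). The rule for new onsets reads: "The physician will document all diseases that occur from the time the trial product is used to the date of completion of its use". This is followed by: "The investigator will observe the patients until the disease is resolved or until two weeks after the end of their participation in the clinical research".
- **Tube removal** (Treatment): feeding goes on at home after discharge, and "the tube will be removed at an outpatient hospital when oral intake is considered sufficient". No date is given for removal or for the last feed.
- **Hazard after removal** (Discussion): in describing the placement technique, the article says that "a tube is fixed to the abdominal wall to prevent peritonitis after removing the feeding tube".
- **Safety as an aim** (Discussion): "we aim to determine the safety and nutritional status of postoperative enteral nutrition". The Hypothesis section also concerns safe administration. Under Follow-up and assessment, "The occurrence of illness and other symptoms will be evaluated as part of the safety assessment", with gastrointestinal symptoms given as the examples.
- **Length of follow-up** (Study design, endpoints, and period): "the follow-up period is 6 months". For patients who stop protocol treatment but stay in the study, the Discontinuing criteria add that "investigation and observation as provided for in the research will be conducted until the end of the follow-up period".
- **Another place where events might be recorded** (Follow-up and assessment): postoperative complications are collected with the surgical information, separately from the safety assessment and with no stated period.

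**The concern.** The recording rule ties the onset window to product use and allows no interval afterwards. Two kinds of event then fall outside it.

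The first is anything that begins after the tube has come out. The article itself names one such event.

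The second is a delayed event in a patient who stopped the product early. That patient remains under observation, but the window for new diseases has already closed. The window is therefore shortest for those who stopped soonest, and some of them will have stopped because of illness or poor tolerance.

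At stake is the safety description, which is one of the trial's stated purposes. An event proportion built on windows of unequal length, where the length depends partly on tolerance, is hard to interpret. Events that are not collected prospectively may not be recoverable later.

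**Working it through.** The plan gives no figure for this window, so the main check sets the sections side by side.

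**1. Events after tube removal.** Let L be the date of last product use, R the date of tube removal and T the onset date of a new disease.

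- The recording rule requires T ≤ L.
- The product is given through the tube (Treatment), so L ≤ R.
- Hence T > R implies T > L, and the event is outside the window.

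This holds whether removal is on the day of the last feed (L = R) or later (L < R). An onset on the day of removal itself is inside the window only if L = R.

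**2. Patients who stop early.** For them L is the day of stopping, and any later onset has T > L. The Discontinuing criteria continue only such observation as the research provides for. The one stated rule for new diseases ends at L, so that clause adds no window of its own.

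The Sample size section shows how many patients might be affected: about 5 excluded for complications, about 2 stopping for recurrence, and 25 − 23 = 2 non-completers among those analysed. That is 5 + 2 + 2 = 9 of 32, or 28%. It is an upper count under those planning assumptions, because some of the 9 may never start the product or may stop late.

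**3. The follow-up sentence.** It runs until the disease resolves or until two weeks after participation ends. Its subject is the disease already documented under the sentence before it, so it sets how long a recorded event is followed and not which onsets are recorded. If it was meant to admit new onsets, it conflicts with that sentence, and the two need to be reconciled.

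**4. Table I.** As it reads here, the row for observation of diseases is marked at POD 0, POD 2 and discontinuation of the trial, with nothing at 2, 3 or 6 months. It also has no mark at POD 28, when the product may well still be in use, so marks may have been lost. The row is supporting evidence at most.

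**5. Illustration of size.** Inputs:

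- n = 25 + 5 + 2 = 32, which reproduces the planned sample size.
- p, the true rate of a post-removal event. The documents give none, so 1%, 2% and 5% are assumed.

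Expected events = n × p. Chance of at least one = 1 − (1 − p)^n.

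| Assumed p | Expected events, n = 32 | Chance of at least one, n = 32 | Chance of at least one, n = 25 |
|---|---|---|---|
| 1% | 0.32 | 1 − 0.99^32 = 28% | 22% |
| 2% | 0.64 | 1 − 0.98^32 = 48% | 40% |
| 5% | 1.6 | 1 − 0.95^32 = 81% | 72% |

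These are chances that an event occurs, not chances that it is lost from the record.

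**The case against.** **The window suits the product.** The gastrointestinal symptoms named as examples would mostly arise while the formula is being given, so an on-product window is a defensible choice for them. Peritonitis is a hazard of the tube, is mentioned once, and appears as something the technique is meant to prevent. This stands as far as it goes. However, the stated aim is the safety of enteral nutrition, which is delivered by that tube, and the gap for early stoppers does not depend on peritonitis.

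**Another route may catch these events.** Peritonitis after removal of a surgically placed tube could well be recorded as a postoperative complication, and a condensed article may leave the period for that item to the full protocol. Table I also marks observation of diseases at discontinuation of the trial, which can fall after last product use. Both points stand. A reader might infer that the rule guarantees a record of 0 in 32 for post-removal events, and the documents do not support that. They support only that such events are outside the stated adverse-event window and that nothing stated ensures their capture elsewhere.

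**The length of the gap is unknown.** A reader might take 2 months as day 60 and 6 months as day 182, and conclude that new onsets go unrecorded for 122 of 182 days (67%). The documents do not support this either. Two months is when the endpoint is assessed, not a stop date for feeding, and Table I still confirms feeding at 3 and 6 months. Unrecorded days are also not a measure of missed events.

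**Bowel obstruction.** It may be tempting to add this to the missed events. The Discussion ties that risk to a jejunal enterostomy, and in this trial the tube is placed from the antrum of the gastric tube, so it is not part of this point.

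**Limited consequence.** There is no comparator and no stated safety threshold. A downward bias of a given size is therefore not shown; only the direction is plausible.

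**Conclusion.** The point holds in a limited form. The stated adverse-event window closes on the last day of product use. Onsets after the day of tube removal, and delayed onsets after early stopping, are outside it, although safety is a stated aim and patients remain in follow-up to 6 months. This rests on the wording of the rule and on the route of administration, not on any assumed date.

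The number of events affected cannot be derived from the documents. It depends on when use and the tube end, on how many events occur, and on how many are picked up as postoperative complications. The range of 28% to 81% in 32 patients depends entirely on the assumed rates of 1% to 5%.

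The primary endpoint, its confidence interval and the sample size do not change. This is a cheap improvement to the safety record and does not undermine the trial's main result.

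**What to change.** In the section on evaluation and reporting of adverse events:

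- Extend the onset window to the later of a short fixed interval after last product use and the same interval after tube removal. The two weeks already used in that section would serve as the interval.
- Apply the same window to patients who discontinue the product early.
- Record the date of tube removal and the onset date of each new disease.
- Ask about new diseases, including tube-site events and peritonitis, at the existing 2-, 3- and 6-month visits that fall in the window, and bring Table I into line.

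This changes data collection only, not treatment. The cost is a reworded sentence and a few form fields at visits already scheduled. The safety result may look slightly less favourable, because somewhat more events will be recorded.
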